#### Training of the first-line managers in the control group

The first-line managers randomized to the control group will receive a 3-h lecture which includes a brief overview of worker health, work stress and the mismatch model [37]. The information includes protective and risk factors in the work environment in relation to occupational stress and CMDs. Basic information about the importance of self-efficacy for mental health is given, and different ways of interacting with and supporting employees with CMDs are reflected upon. The lecture also includes advice about communication, with focus on general communication skills: listen actively and attentively; encouraging the employee to talk; summarizing and checking your understanding of what has been said; observing and describing the employee’s feelings without judgment [33].

### Measurements

Data will be collected from registers, self-reported questionnaires, text messages and qualitative interviews. Register data on sick leave will be collected from the employer’s register, and the Micro Data for the Analysis of Social Insurance register (MiDAS) provided by the SSIA. Register data on employee characteristics will be collected from the Longitudinal integrated database for health insurance and labor market studies (LISA) [38]. Web-based questionnaires will be administered at baseline and at 6- and 12-month follow-up. Text messages will be sent every fourth week to the employees during a 12-month period. A 36-month follow-up of sick leave based on register data is planned.

### Primary outcome

#### Sick leave

The primary outcome is the total number of days of sick leave due to CMDs during the 12-month follow-up. Data will be collected for individuals from the participating companies’ (employers’) registers (covering the first 14 calendar days of sick leave) and from the MiDAS register (sick leave ≥15 days) covering part-time (defined as 25, 50 or 75% of full-time) and full-time. Sick leave due to diagnoses other than CMDs will also be included. Data will be collected from baseline until the 12-month follow-up and for the 24 months preceding baseline. The primary outcome is based on data from the employers’ and MiDAS registers, limiting missing values during follow-up.

### Secondary outcomes

Data on the secondary outcomes will be collected by means of self-reported questionnaires and text messages.

#### General health and psychological symptoms

Self-rated general health is measured with a single item from the Short-Form Health Survey with 5-point response anchors, from (1) “excellent” to (5) “bad” [39]. The presence and severity of depression (7 items) and anxiety (7 items) are assessed by the validated Hospital Anxiety and Depression Scale, which is a 14-item self-reported questionnaire [40, 41]. The response format is a 4-point scale, ranging from 0 (not at all) to 3 (nearly all the time), with higher scores indicating higher levels of depression and anxiety. Self-reported exhaustion will be assessed by four items of the self-rated exhaustion disorder (s-ED) scale [42], that has demonstrated construct and predictive validity. The response format is yes/no [42]. Work stress is measured by a single item with a 5-point response scale, ranging from (1) “not at all” to (5) “very much” [43], administered as a text message.

#### Work performance impairment and work ability

Work performance impairment will be evaluated by two items administered as text messages: one item about impairment of work performance due to health problems (presenteeism), and one item about work environment problems. These items have been developed, modified and validated [44] and were inspired by the Work Productivity Activity Impairment questionnaire [45]. The first item, impairment of work performance due to health problems, is assessed by the following question: “During the past four weeks, how much did your health problems affect your performance while you were working?”. The respondents are asked to rate how their health-problems affect their work performance on a scale ranging from 0 indicating that health problems had no effect on their work, to 10, indicating that health problems hindered them from working at all. The second item about work-environment problems is measured by the question: “During the past four weeks, how much did work environment problems affect your performance while you were working?”. The response format is a scale ranging from 0 to 10, with higher scores indicating that work environment problems prevented respondents from working. The items have been tested in a Swedish setting and shown reliable psychometric properties (test-retest ICCs with 95% CIs for health related and work-environment production loss, respectively: 0.90, (CI; 0.74–0.98); 0.91, (CI; 0.79–0.98)) [46].

Work ability will be measured by three items of the Work Ability Index [47]. Two items refer to perceived work ability in relation to the physical and mental demands of the work. The response format is a five-point scale, ranging from “very bad” to “excellent”. The third item assesses the employee’s own beliefs about his/her work ability: “Do you believe that – from the standpoint of your health – you will be able to do your current job two years from now?” with response format “unlikely”, “not certain”, “relatively certain” [47].

#### Psychosocial work environment

The Copenhagen Psychosocial Questionnaire (COPSOQ) III, Swedish standard version [48], is used for assessing *demands at work* by quantitative and emotional demands. *Interpersonal relations and leadership* are assessed by recognition and quality of leadership; *work-individual interface* is measured by commitment to the workplace and work-life conflict. These scales are measured at baseline and at 6- and 12-month follow-up. The response format is a Likert scale with five levels (0, 25, 50, 75, 100), with higher scores indicating higher work demands, better interpersonal relations and leadership, and for the work-individual interface, higher scores indicate better commitment to the workplace and worse work-life conflict.

The impact of private life on work is measured by the single item: “Do the demands of your family or spouse/partner interfere with your work-related activities?” from the General Nordic Questionnaire [49, 50] with the response anchors “Very seldom or never” to “Very often or always”.

#### Intermediate outcomes

General self-efficacy measures the employee’s belief in his/her ability to cope with the current situation, to mobilize motivation and act upon demands in different situations. It is positively correlated with mental work capacity. In this study, general self-efficacy is included to clarify how the intervention is working and is measured by a Swedish-validated version of the General self-efficacy scale [51], at baseline and at 6- and 12-month follow-up. Responses are given on a four-point Likert scale ranging from (1) “not at all true” to (4) “exactly true”. A validated single-item measure of self-efficacy is also used: “I am confident in my ability to solve problems that I might face in life”. The response format is a ten-point scale from (1) “totally disagree” to (10) “totally agree” [52].

In addition, problem-solving might lead to a better perception of influence at work, and manager support, measured by COPSOQ III subscales Influence at work, and Social support from supervisor [48]. Influence at work is assessed by four questions of Influence at work scale (e.g. Do you have any influence over what you do at work?). Manager support is assessed by two questions of the social support from supervisor scale (e.g., How often is your immediate superior willing to listen to your problems a work, if needed?).

#### Prognostic factors

A variety of prognostic factors for the risk of future sick leave due to CMDs will be measured. Employees’ personal characteristics (e.g. age, gender, marital status, educational level, profession) and workplace characteristics (e.g. sector) will be collected from the baseline questionnaire and the LISA and MiDAS registers.

Employees’ psychosocial safety climate (PSC) will be measured at baseline. PSC focuses on the senior management’s role in creating a healthy work environment and refers to the employees’ perceptions of the organization’s psychosocial health climate, e.g. guidelines, practices and procedures used to establish and maintain a psychosocial safe and sound work environment [53]. Further, the concept reveals whether the senior management supports stress prevention at work. The four-item version of the valid and reliable Psychosocial Safety Climate [54] will be used, using a 5-point scale ranging from (1) “strongly disagree” to (5) “strongly agree”. Average scores > 12 indicate good occupational safety and health [55].

Information about workplace adjustments (e.g. changes in work tasks, working hours, change of department) and co-interventions (e.g. psychological counselling, and if so, number of sessions, use of antidepressants, general health care consumption, contact with the occupational health service) will be collected from the employees at baseline and at 6- and 12- month follow-up.

The first-line managers’ personal characteristics (e.g. age, gender, marital status, education) and workplace characteristics (e.g. sector, profession, number of employees, leadership network, leadership training) will be collected. In addition, the first-line managers’ self-efficacy (single item), problem-solving confidence [56], leadership support or supervision, and perceived ability to support employees with CMD, will be measured at baseline and after 12 months.

### Process evaluation

A process evaluation will be conducted alongside the cluster-randomized controlled trial, as recommended by Moore et al. [57]. The process evaluation is based on the theoretical framework by Linnan and Steckler [58] and the Consolidated Framework for Implementation Research (CFIR) [59]. The process evaluation will examine the study’s core intervention activities (i.e. identification of early signs of CMDs, information to first-line managers about worker health and early signs of CMDs, training of first-line managers in problem-solving conversation and communication) with regard to 1) reach, 2) fidelity, 3) dose delivered and dose received, 4) satisfaction and context. Process-evaluation data will be collected at employee- and first-line manager-level, at baseline and during and post-intervention, by means use of self-reported questionnaires and semi-structured interviews.

*Reach* is measured at employee- and first-line manager-level. For employees, reach is defined and measured as the proportion of all employees eligible for inclusion who agree to participate in the study. The first-line managers attendance in the training and booster sessions will be measured by attendance and satisfaction.

*Fidelity* is about adherence to the study protocol and intervention delivery. It is assessed as by whether, and to what extent, it was possible for the first-line manager to deliver the intervention as intended. The first-line managers will provide data on their adherence to the manual for each of their employees during the intervention period.

*Dose delivered* is operationalized as number of times the first-line manager meets with the employee including number of follow-up sessions, as face-to-face meetings or telephone follow-ups, and the content of the meetings and follow-ups. *Dose received* is assessed by to what extent the employee receives the problem-solving intervention, in terms of numbers of meetings and follow-ups with the first-line manager. The employees are asked to rate the quality of the meetings with their first-line manager.

*Satisfaction and context* among first-line managers and employees are measured with self-reported questionnaires (first-line managers) and qualitative semi-structured interviews (first-line managers and employees). Satisfaction is defined as how participation in the intervention is perceived, for example the perceived benefits of taking part, or the resources needed for the delivery of the intervention. Context is operationalized as the perceived barriers and facilitators which influence the implementation of the intervention. First-line managers will be asked to rate the resources available for them for delivering the intervention, e g. time, managerial support. The interview guides will be developed by the research team. Questions specifically related to the context will be based on the CFIR guide to enable a systematic identification of barriers to and facilitators of the intervention [59, 60].

### Data analysis

Multilevel analyses for cluster-randomized trials will be conducted. To investigate the effectiveness of the primary and secondary outcomes, we will perform intention-to-treat analyses using linear and generalized models taking the multilevel nature into account. The primary outcome will be analyzed using generalized estimating equations with independent correlation structure and robust variance estimation.

The primary outcome (number of days of sick leave due to CMDs during the 12-month follow-up) will be analyzed from baseline during the 12-month follow-up. The parameter of interest will be the group allocation. The analysis will, for example, be conducted using regression-based methods that allow the intra group correlation induced by the clustered randomization design. Group-based trajectory models will be used to map the developmental course of symptoms, and to assess the heterogeneity in response to clinical interventions [61].

A longitudinal analysis of days of sick leave and of secondary outcomes can also be conducted, given the intra-person longitudinal nature of the data. This can be done at day, week, month or quarter level, depending on the granulation of the data and the nature of the outcome of interest.

Semi-structured interviews collected as process-evaluation data of perceived barriers to and facilitators of the intervention will be analyzed by qualitative content analysis [62] or thematic analysis [63].

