### Randomization and blinding

The current study is designed as a two-armed cluster-randomized controlled trial. The randomization of participants is computer-generated, stratified by company, and takes place at the level of first-line managers. They are allocated at the individual level to intervention- or control group by means of computer-generated random numbers with allocation ratio 1:1. The random allocation sequence is generated by an independent statistician. The first-line managers will be enrolled and informed about their allocation by a research assistant.

To avoid contamination, the first-line managers in the intervention arm are instructed to talk and discuss the intervention only with each other and the project team. The first-line managers are not blinded to allocation since they will know about their participation in the problem-solving training (intervention) or the workshop (control condition).

Eligible employees follow the randomization of their first-line manager and are randomized before providing informed consent. All employees, irrespective of whether they are in the intervention- or control group, receive the same information about the study. The information contains details about randomization but not about the content of the two arms, i.e. the employees are blinded for their group allocation. Research assistants, blinded to the first-line managers’ and employees’ randomization, will manage the screening procedure and the outcome assessments (i.e. administration of baseline, follow-up questionnaires and text messages). The statistical analyses will be performed by an independent statistician who will be blinded for the participants’ randomization (both first-line managers and employee).

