#### Statistical power

By sampling 38 clusters (19 clusters in the intervention arm and control arm respectively) with an average of three employees in each cluster, the study population is estimated to be a total of 114, with 57 employees in the intervention group and the control group respectively. With these numbers it will be possible to achieve about 80% power to detect a difference of 30% in number of days of sick leave during the 12-month follow-up, assuming that the mean number of days in the control group is 108 [14]. The standard deviation of sick leave days was 60 days [10]. The intra-cluster correlation was set to 0.015 and a significance level of 0.05, two-sided test.

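### The primary GEE names a robust variance on 19 managers per arm but no small-sample correction or t reference; in its ordinary form it would test at about 6.4% instead of 5%

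*Protocol article*

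**What the plan says.** In the protocol article, Data analysis, the primary outcome (sick-leave days over 12 months) is assigned to "generalized estimating equations with independent correlation structure and robust variance estimation". Statistical power sets the number of independent units: "By sampling 38 clusters (19 clusters in the intervention arm and control arm respectively"), "with an average of three employees in each cluster", giving "a total of 114, with 57 employees in the intervention group and the control group respectively". Significance is two-sided at 0.05 and the intra-cluster correlation is 0.015.

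Randomization and blinding states that randomization "takes place at the level of first-line managers" and is stratified by company, so the manager is the cluster.

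The article does not say whether the robust variance is corrected for few clusters. It also does not give the reference distribution, the link function, the spread of cluster sizes, or whether company enters the model.

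**The concern.** With an independence working correlation, the sandwich variance is the only part of the analysis that accounts for clustering. Its justification is asymptotic in the number of clusters, not of employees. With few clusters the residuals are too small because the model has been fitted to them, so the variance is biased downward. A normal critical value also ignores the uncertainty in the variance estimate itself. Both errors push the same way, towards too many rejections and too short a confidence interval.

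With 19 managers per arm this affects the confirmatory test. Unqualified robust variance can be implemented in several ways. If the choice is still open when results are seen, it could decide significance in a borderline case.

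**Working it through.** **Inputs from the protocol article (Statistical power):** K = 19 clusters per arm, mean size m = 3, ICC = 0.015, control mean 108 days, difference 30% (0.30 × 108 = 32.4 days), SD 60, two-sided 0.05.

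**1. The plan's own power figure.**
- Design effect: 1 + (3 − 1) × 0.015 = 1.03.
- SE of the difference: 60 × √(2 × 1.03 / 57) = 11.41 days.
- Ratio: 32.4 / 11.41 = 2.84.
- Power with a normal reference: Φ(2.84 − 1.96) = 81.1%. The stated figure of about 80% is reproduced.

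**2. Error rate of the ordinary sandwich, equal clusters, identity link (closed form).**
- In each arm the uncorrected variance has expectation (K − 1)/K of the true variance. The SE ratio is √(18/19) = 0.973, so the SE is 2.7% too small.
- Degrees of freedom: 38 − 2 = 36.
- Normal reference: P(|t₃₆| > 1.96 × 0.973) = P(|t₃₆| > 1.908) = **6.44%**. Simulation (40,000 runs) gives 6.4%.
- t on 36 df without correcting the variance: 5.6%.

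**3. Sensitivity to features the article does not give.** These are simulations under no effect with the ordinary sandwich and a normal reference: 40,000 runs per normal scenario and 10,000 per zero-inflated scenario. Cluster-size spread, zero fraction (30% or 70%), shape of the non-zero days and link are assumptions. Normal outcomes were run at ICC 0.015 and 0.05, the others at 0.015.

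| Scenario | True alpha |
|---|---|
| Normal outcome, unequal sizes | 6.7% to 7.6% |
| Zero-inflated outcome, identity link | 6.1% to 6.5% |
| Zero-inflated outcome, log link | 6.5% to 8.5% |

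With 70% zeros and a log link, alpha is 8.3% with equal clusters and 8.5% with unequal ones. In the latter case the SE is about 11% too small. These runs ignore the company strata.

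**4. Effect of a correction.** For equal clusters, Kauermann-Carroll multiplies the variance by K/(K − 1) and Mancl-DeRouen by the square of that factor.

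| Method | Alpha, equal clusters | Alpha, all scenarios | Power, 19 per arm | Power, 20 per arm |
|---|---|---|---|---|
| Kauermann-Carroll, t | 5.0% | 4.7% to 6.6% | 78.9% | 81.1% |
| Mancl-DeRouen, t | 4.4% | 4.1% to 6.0% | 77.3% | 79.6% |

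The t reference has 36 df with 19 clusters per arm and 38 df with 20.

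**5. Company strata.** A separate check used 20,000 runs, the ordinary sandwich with a normal reference, equal clusters of three, and an analysis that omits company. With an assumed four companies, alpha is 6.6%, 6.1%, 5.6% and 4.9% when company accounts for 0%, 1%, 3% and 5% of the variance. With two companies and 5% it is 5.5%.

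**The case against.** The strongest objection is that the defect is read from silence. A reader might infer that the protocol commits to an uncorrected sandwich with a normal reference, and hence that its confirmatory test is invalid. The text does not support this. A Kauermann-Carroll or Mancl-DeRouen variance with a t reference is also robust variance estimation, and a condensed article may leave that detail to a statistical analysis plan. This stands, and it makes the point conditional. It does not remove it: the article chose the working correlation and the variance type, and that pairing needs a correction at 19 clusters per arm.

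Second, the inflation is small on the stated inputs, and the higher values need assumptions. This also stands. Many zeros are plausible because employees on sick leave at entry are excluded, but the planning values point the other way. If a fraction p has any days, CV² is at least (1 − p)/p. Taken together, 60 and 108 give CV² = 0.309, so p is at least 1/1.309 = 76%, or at most 24% zeros. Unequal sizes are likely, since size depends on who screens positive and consents, but their spread is not given.

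Third, omitting company from the analysis after stratifying on it makes the test more conservative and can cancel the inflation. This is true under the assumed company variances. Whether company is adjusted for is not stated, and adjusting would lower the cluster-level degrees of freedom below 36. Relying on an unknown offset is not a way to hold the level.

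Fourth, a corrected sandwich does not fully cure the worst scenarios: up to 6.6% remains with Kauermann-Carroll. That is why the permutation test is part of the fix.

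**Conclusion.** The point holds conditionally. If the primary GEE is run with the ordinary sandwich and a normal reference, its SE is about 2.7% too small and its true two-sided level about 6.4%, assuming 19 equal clusters of three per arm and an identity link. Under assumed unequal sizes, many zero-day employees and a log link it reaches roughly 8 to 8.5%. Omitting company strata from the model could bring it back towards 5%.

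The documents do not show that the test as finally specified fails its level. They show an estimator that, left as named, allows an implementation that does. The excess is modest, so this is a correction worth making and not a fatal flaw. Confidence is moderate, because the statistical analysis plan is not shown and may already settle it.

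**What to change.** State that the primary GEE uses a Kauermann-Carroll bias-corrected sandwich variance with a t reference on the number of clusters minus the number of cluster-level parameters (36 df before any company terms). State also whether company enters the model. Add a supporting permutation test that re-randomises managers within company. It follows the randomization actually used and does not depend on large-sample behaviour when many employees have zero days.

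If a statistical analysis plan already specifies an equivalent correction, citing it is enough. Either way, fix the choice before unblinding.

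The cost is a sentence or two and options available in standard software. Intervals become slightly wider. Power at the planning values is 78.9% instead of 81.1%, or 77.3% if Mancl-DeRouen is preferred. One more manager per arm (20, about 120 employees) would bring these to 81.1% and 79.6%.
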